**Protocol version: 16**

Executive Summary and Organizational Overview:

Developing new interventions that incorporate the “diverse needs and circumstances of people with mental illness,” particularly in primary care and community settings, is a key NIMH strategic objective. Prevention of mental disorders has become a priority for the NIMH, which emphasizes the importance of developing “new and better interventions” to “...preempt the occurrence of disease.” These interventions must (1) work in multiple and diverse settings (e.g. primary care); (2) be suitable for delivery outside of traditional mental health systems (3) use new technologies; (4) build on previous clinical trials; (5) reduce identified disorders/enhance functional outcomes; (6) include families and (7) be tailored to the individual. Despite these NIMH guidelines, while primary care physicians remain the first line providers for at-risk adolescents, there is no widely available, low cost and culturally acceptable preventive approach that targets depression in primary care settings. To address this gap and specified NIMH priority, [name] developed and conducted a phase 2 clinical trial of a primary care Internet-based depression prevention intervention (CATCH-IT, Competent Adulthood Transition with Cognitive Behavioral Humanistic and Interpersonal Training). In this study, the high intensity arm (i.e., motivational interview + internet site) demonstrated significant reductions in depressed mood and increases in protective factors (social support, motivation) and lower incidence of depressive episodes over 12 months (7% versus 28%), compared to the low intensity arm (internet site referral + only physician brief advice). We now propose the next step study, a phase 3 efficacy study. In this 5-year, two-site randomized clinical trial, we propose to test the efficacy of the CATCH-IT primary care/Internet based

[figure not shown][figure not shown]

symptoms, depressive diagnoses, other mental disorders, and on measures of role impairment in education, quality of life, attainment of educational milestones, and family functioning; and (d) conduct **exploratory** analyses to examine the effectiveness of this intervention program, moderators of protection, and potential ethnic and cultural differences in intervention response.

## **2. Study Hypothesis and Specific Aims (purpose, objectives)**

**Significance:** Prevention of mental disorders has become a key priority for the NIMH, but we have no widely available public health strategy to reduce morbidity and mortality. We developed a primary care/Internet based depression prevention intervention strategy intended to meet the NIMH call for developing “new and better interventions” for “diverse needs and circumstances” to “...preempt the occurrence of disease.” These interventions must (1) have broad “reach” into at-risk populations; (2) work outside of traditional mental health systems; (3) use new technologies; (4) build on previous clinical trials; (5) reduce identified disorders/enhance functional outcomes; (6) include families; and (7) be personalized. Primary care for adolescents provides a nearly untapped new opportunity to build cost-effective prevention strategies for depression. **Innovation:** Based on face-to-face manual-based interventions of demonstrated efficacy, the CATCH-IT intervention (Competent Adulthood Transition with Cognitive Behavioral Humanistic and Interpersonal Training (CATCH-IT) represents a paradigm shift. Key innovations include: (1) it is the first of its kind, a public health adolescent depression prevention strategy (low cost, easily disseminated, acceptable and feasible primary care/Internet model); (2) it combines a brief primary care-based motivational program with an Internet-based self-directed Cognitive Behavioral (CBT) and Interpersonal Psychotherapy (IPT) approach to address the key barrier of engagement/adherence; (3) it targets both adolescent and parent vulnerability and protective factors in separate interventions, using an ecological model; (4) it is personalized to the presence of parental depression and ethnicity/culture, key moderators in prior studies; and (5) it uses media based learning strategies including music, videos, and stories to convey learning. We demonstrated feasibility and potential efficacy in a randomized clinical trial in 12 primary care practices in 4 states/5 health systems (40% ethnic minorities) supported by a K-08 Award (2006), a NARSAD foundation Young Investigator Award (2004), and a RWJ Foundation Depression in Primary Care value grant (2005). In this study, CATCH-IT 3 demonstrated significant reductions in depressed mood (vulnerability), increased social support (protection), and reduced depressive episodes at 12 month follow-up (6.98 versus 27.50, p-value =0.013). **Approach:** In this application, we propose the next step study, a 5-year, two-site (University of Illinois at Chicago/Access Healthcare and Wellesley College/Harvard Vanguard) randomized clinical trial (analytic site is Northwestern University), to test the efficacy of a second generation CATCH-IT 3 (revised to include engaging media based learning) prevention intervention against Attention Monitoring and Psycho-education (HEALTH EDUCATION) in preventing the onset of depressive episodes in an intermediate to high risk, geographically representative sample of adolescents aged 13-18. We plan to: (a) identify high risk adolescents based on elevated depressed mood scores (cut-off set to maximize sensitivity and specificity for future episode); (b) recruit 400 (200 per site) of these at-risk adolescents to be randomized into either the CATCH-IT 3 or the HEALTH EDUCATION group; (c) assess at baseline and at 2, 6, 12, 18 and 24 months post intake on measures of depressive symptoms, depressive diagnoses, other mental disorders, and on measures of role impairment in education, quality of life, attainment of educational milestones, and family functioning; and (d) examine predictors of intervention response, and potential ethnic and cultural differences in intervention response.

**Aim 1:** To determine whether the CATCH-IT 3 depression prevention intervention prevents or delays major depressive episodes, as well as non-affective disorder episodes, compared to HEALTH EDUCATION.

**Hypothesis 1:** Compared to youth in the HEALTH EDUCATION condition, youth assigned to CATCH-IT 3 will have a lower hazard ratio of major depressive episodes and non-affective disorder episodes over 2 years.

**Aim 2:** To determine if participants in the CATCH-IT 3 group exhibit more rapid favorable changes of depressive symptoms/and or vulnerability/protective factors compared with the HEALTH EDUCATION group.

**Hypothesis 2:** Compared to youth in the HEALTH EDUCATION condition, youth in the CATCH-IT 3 program will demonstrate a steeper slope of improved symptoms through growth curve analysis and fewer depressed days over two years.

**Aim 3:** To determine if participants in the CATCH-IT 3 program report lower perceived educational impairment, greater quality of life, greater health-related quality of life, and lower incidence of other mental disorders (anxiety, substance/alcohol use) as compared to participants in HEALTH EDUCATION. **Hypothesis 3:** Compared to youth in the HEALTH EDUCATION group, youth in the CATCH-IT 3 program will demonstrate more rapid benefits in reduced educational impairment, improved quality of life, and fewer disorders, as shown through steeper changes in slopes based on growth curve analysis over 2 years.

**Aim 4:** To determine for whom (moderators) and how (mediators) the CATCH-IT 3 program works in this population (Figure 1). **Hypothesis 4A:** CATCH-IT 3 effects will be moderated by six domains: (1) demographic/cultural factors, (2) vulnerability factors/adverse events, (3) motivation, (4) physician relationship, (5) parent/child co-morbid psychopathology, and (6) treatment. **Hypothesis 4B:** The relation between CATCH-IT 3 participation and reduction in depressive episodes will be mediated by adherence to the Internet and motivational interview fidelity as they alter vulnerability factors (e.g. motivation, cognition and social support) and responses to adverse events, which in turn impact the likelihood of episodes.

**Exploratory Aim 1:** To determine the implementation feasibility of the intervention from the physician/nurse practitioner and office nurse/medical assistant perspective as well to describe the practices in relationship to the medical home model.

**Exploratory Aim 2:** To determine whether CATCH-IT 3 has a favorable cost-benefit ratio and/or cost effectiveness of <\$50,000/disability adjusted life year compared to the HEALTH EDUCATION group.

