## **Sample Size and Statistical Power**

**Aim 1:** We conducted a series of power/sample size calculations through a SAS macro ([name], 1995) under realistic alternatives to address impact on MDE. We require 200 randomized subjects per intervention condition to achieve 80% power based on a conservative application of our pilot study findings from the CATCH-IT trial. These calculations assume that in the control group 72% are free from depression after one year follow up and the second year continues to follow the same exponential rate for controls; for intervention the hazard is a constant ratio of 0.62, and an attrition rate of 7% for each of the first 4 quarters and 2% for each of the second 4 quarters. Note that the estimated hazard rate of 0.62 is 2/3 of that we observed in this previous study. There are concerns raised about the use of pilot study data to assess power, even using a

lower value than we observed, so we conducted other power calculations based on the data from a similar study. In their study, they found a departure from exponential and disproportional hazards of intervention over time. Assuming the same attrition rate as we found above, a study with 400 randomized subjects would produce 80% power when the effect of CATCH-IT 3 was only 60% at every interval of time relative to the CBT hazard rate in the Clarke's study. Thus we expect to have sufficient power even if the overall benefit is 60% that obtained by Clarke.

**Aims 2 and 3:** We will examine changes in the growth curve for depressive symptoms and quality of life over 6 measures. We have 80% power to detect a modest effect size of 0.25 by the last time point, accounting for 75% reliability in the intercept ([www.psmg.usf.edu/PowerCal/case0.html](http://www.psmg.usf.edu/PowerCal/case0.html)).

**Aim 4:** Using mean and standard deviation values from our previous educational impairment data as an illustration of moderator analyses with M=11.3 (SD=3.6) and M=9.9 (SD=3.4), with power of 0.80, alpha level of 0.05, and 10% attrition, 109 participants are needed for each group for a total of 218 participants. Thus we have sufficient power to detect moderate to large interactions with intervention.

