**Why a stream-lined assessment battery?** The goal of this study is to examine the efficacy of an intervention with very limited person-to-person contact in realistic community settings with a population of primary care patients comparable to the general population of adolescents. We believe, based on our prior survey research, that extensive person-to-person psychological evaluation may alienate many potential study participants. We are thus only conducting a single face-to-face assessment meeting at baseline, and will conduct subsequent assessments via the telephone.

**Why assess parents for depressive symptoms?** Although the focus of the CATCH-IT 3 intervention is on preventing youth depression, for several reasons we are also assessing parental depressive symptoms. First, parental depression is a significant predictor of depression in adolescence. Second, in a multi-site depression prevention study targeting at-risk adolescents, current parental depression was found to modify intervention effects, such that the intervention only decreased the incidence of depression in youth whose parents were not currently depressed. Finally, studies of family-based prevention programs indicate that, in addition to decreasing risk for depression in the youth targeted by the intervention program, these prevention efforts also have decreased depressive symptom levels in parents. We will assess depressive symptoms in parents at each time point and offer parents Internet based resources if they are experiencing depressed mood. We will also examine the moderating and mediating influence of parental mood on outcome.

**Why a two-year follow-up?** Effects from other prevention programs for youth depression have diminished over 22 months. Also, effects from some prevention programs for youth depression have *increased* over time. We will follow participants for 2 years after intake to detect both initial and more enduring aspects of the intervention. Extended follow-up is especially important in *prevention* outcome interventions, because by definition the participants enter this investigation when they are not in an episode of depression and must be followed prospectively to determine if the experimental intervention minimizes or eliminates future episodes.

**Bo**

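### Moderator analyses are labelled exploratory in two sections but form a numbered, six-domain hypothesis with its own power claim in Aim 4; they need one status

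*Protocol*

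**What the plan says.** Exploratory status:
- Item (d) of the Executive Summary, repeated in the Summary under Methods, Research Design, is to "conduct exploratory analyses to examine the effectiveness of this intervention program, moderators of protection", together with ethnic and cultural differences in response.

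Hypothesis status:
- Section 2 has a parallel item (d) without the exploratory label: "examine predictors of intervention response, and potential ethnic and cultural differences in intervention response".
- Aim 4 in Section 2 is "To determine for whom (moderators) and how (mediators) the CATCH-IT 3 program works in this population". Hypothesis 4A follows: "CATCH-IT 3 effects will be moderated by six domains". The six domains are demographic/cultural factors, vulnerability and adverse events, motivation, physician relationship, parent and child psychopathology, and treatment. None is ranked and none is given a direction.
- Section 2 then lists two aims headed Exploratory. The first is "To determine the implementation feasibility of the intervention from the physician/nurse practitioner and office nurse/medical assistant perspective" and the second concerns cost-effectiveness. Neither covers moderators.
- The Moderator analysis paragraph under Data analysis plans subgroup analyses and interaction tests in all six domains.
- Sample Size and Statistical Power, Aim 4, gives a calculation "with power of 0.80, alpha level of 0.05, and 10% attrition", arrives at 109 per group (218 in total), and concludes that power is sufficient for interactions of moderate to large size.

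Prior basis:
- Section 2 (Innovation) names both parental depression and ethnicity/culture as important moderators in earlier studies.
- The Rationale for Selection of Subject adds a specific result from a multi-site prevention trial: "current parental depression was found to modify intervention effects".

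**The concern.** The label decides what may be concluded. If moderation is exploratory, a significant interaction is a lead for later work. If it is a numbered aim with a stated hypothesis and a power claim, the same result can be reported as support for that hypothesis. Because Hypothesis 4A spans six unranked domains without direction, an interaction in any of them, of either sign, could be read as partial support. What is at stake is the conclusion on who benefits, which could affect who is later offered the program.

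**Working it through.** **1. The plan's own Aim 4 figure.** Inputs from Sample Size, Aim 4: means 11.3 (SD 3.6) and 9.9 (SD 3.4), power 0.80, alpha 0.05 (taken as two-sided; the protocol does not say), attrition 10%.
- Difference = 11.3 − 9.9 = 1.4. Pooled SD = √((3.6² + 3.4²)/2) = 3.50. Standardised difference = 0.40.
- n per group = 2 × 3.50² × (1.960 + 0.842)² / 1.4² = 98.2, so 99.
- 99 × 1.1 = 109, the stated figure (99/0.9 would give 110).

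The figure reproduces, but as a two-group comparison of means. It is not an interaction calculation, so it does not by itself support the conclusion about interactions.

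**2. Power for an interaction of that size.** Assume a balanced binary moderator, 1:1 allocation and an interaction (difference between two treatment effects) of 1.4 points. Then SE = 4 × 3.50/√N, and power = Φ(1.4/SE − 1.96).

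| Analysed N | Basis | Power |
|---|---|---|
| 400 | no attrition | 52% |
| 360 | 10% attrition (Aim 4) | 47% |
| 276 | Aim 1 attrition: 400 × 0.93⁴ × 0.98⁴ | 38% |

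With 360 analysed, the smallest interaction detectable with 80% power is 0.59 SD. An interaction of 1.4 points would need about 786 analysed.

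**3. Chance of at least one apparent moderator.** Assume no true moderation, one test per domain, each at 0.05, all independent.
- 1 − 0.95⁶ = 0.265, about 26%.
- For comparison, the two moderators named in Section 2: 1 − 0.95² = 0.098, about 10%.

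**4. Could one moderator be made confirmatory on the Aim 1 hazard?** Take from Sample Size, Aim 1, 80% power for a hazard ratio of 0.62 with 400 randomised; two-sided 0.05 is assumed.
- 80% power means |ln 0.62|/SE = 1.960 + 0.842 = 2.802.
- With a balanced binary moderator the SE of the interaction is twice that of the main effect. For a ratio of hazard ratios also equal to 0.62, the standardised effect is 2.802/2 = 1.401.
- Power = Φ(1.401 − 1.960) = Φ(−0.559) = 0.29.
- If the moderator is present in 30% (assumption), the SE factor is √(1/0.3 + 1/0.7) = 2.18, and power = Φ(2.802/2.18 − 1.960) = 0.25.
- For 80% power with a balanced moderator, the ratio of hazard ratios would have to be about 0.62² = 0.38.

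**The case against.** The strongest reply is that this is a labelling slip. The protocol nowhere says that a significant interaction will be claimed as confirmed. The 0.05 in the Aim 4 paragraph is an input to an illustrative sample size, not a decision rule. Ranking and multiplicity rules often sit in a statistical analysis plan, which is not shown. All of that is correct, and the absence of multiplicity rules is not raised here. The reply does not remove the conflict: the protocol's own sections disagree on the status of the analyses, and an analysis plan that adds error control would leave those statements in place.

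Several stronger readings are tempting but unsupported:
- **That the protocol's evidence singles out one moderator.** Section 2 names two, parental depression and ethnicity/culture. Parental depression is only the one with a specific effect-modification result described.
- **That parental mood is treated no differently from the rest.** The Rationale gives it a paragraph of its own and a commitment to examine it as moderator and mediator.
- **That Hypothesis 4A is directional.** It asserts moderation without direction.
- **That the false-positive chance is 46% or more, from 12 or more tests.** This needs about two variables in every domain. The visible tables do not show that: treatment has one instrument, and no physician-relationship measure can be read.
- **That item (d) demotes the primary question by listing effectiveness as exploratory.** The same summaries state the efficacy test plainly, so this is loose wording.

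**Conclusion.** The point holds as a contradiction in status. Moderators are exploratory in the Executive Summary and Research Design, yet a numbered aim with an unranked six-domain hypothesis and an interaction-power claim in Section 2 and the sample size section.

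On the hypothesis-testing reading, the chance of at least one spurious moderator is about 26%. That rests on independence and one test per domain. Correlation among the measures would generally lower it; several variables per domain would raise it. That such a result would be reported as confirmation is an inference from the wording of the aim, not something the protocol states.

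A reader might also infer that parental depression should be promoted to a single confirmatory test. The protocol's own power assumptions argue against that: about 29% power for an interaction as large as the assumed main effect, with a balanced moderator, and about 25% with a 30% share.

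**What to change.** Use one status throughout, the one that the Executive Summary and Research Design already state:
- **Section 2:** label the moderator part of Aim 4 and Hypothesis 4A exploratory, and make item (d) agree.
- **Moderator analysis paragraph:** say that all interaction estimates will be reported with confidence intervals as hypothesis-generating. Parental depression and ethnicity/culture may be listed first as the moderators with a stated prior basis, but without a confirmatory 0.05 test for either.
- **Sample Size, Aim 4:** describe the 109 per group as a two-group comparison, and drop the statement that power for interactions is sufficient or replace it with the detectable interaction size.
- **Executive Summary and Research Design, item (d):** keep the exploratory label, and tidy the reference to effectiveness so that it cannot be confused with Aim 1.

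The change is to wording only and needs no new data. The cost is that findings on who benefits can no longer be presented as tests of a hypothesis.

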### **3. Background and Significance**

#### **a. Significance of Research Project**

**We have no public health strategies to prevent depressive disorder in adolescents (importance):** The lifetime prevalence of major depressive disorder in adolescents aged 15-17 is 14%, and an estimated 20% of adolescents will experience depression by age 17, with considerable long-term impairment and mortality. Although efficacious psychosocial and pharmacological treatments for adolescent depression have been demonstrated, any single approach only helps about 50-75% of those treated. Furthermore, adolescents have low rates of care seeking, receiving high quality treatment (35% and 20%), and completing referrals for psychotherapy (30%). Therefore, prevention of depression in high-risk individuals may be more cost-effective and less distressing than waiting for the condition to appear and then trying to treat a full depressive episode. We now have substantial evidence that cognitive behavioral approaches may prevent adolescent depression, but we have no public health strategy to deliver these approaches to the general population.

**CATCH-IT provides an entirely new prevention strategy for mental disorders to address five key barriers in the field (improving scientific knowledge and medical practice):** To address (1) cost, difficulty in distribution and low acceptability of high fidelity interventions (face-to-face delivery), CATCH-IT delivers a high fidelity intervention via the Internet and primary care in teen-friendly language. For (2) lack of motivation and engagement, we use a social marketing and motivational interviewing strategy. With respect to (3) lack of targeting epidemiologic context including family, CATCH-IT targets the multiple etiological elements acting either in concert or in combination, including negative cognitions, poorer social skills, stressful events, subsyndromal depressive symptoms, and the absence of protective factors (e.g., high self-esteem, coping skills) by engaging both parent and adolescent with distinct behavior change programs. In terms of lack of (4) cultural relevance and (5) multi-modal learning opportunities, CATCH-IT uses a multi-channel learning process and culturally relevant lessons, stories and music, based on face-to-face manual-based interventions of demonstrated efficacy. **Should this intervention prove efficacious, the public would have the first efficacious, low-cost and acceptable depression prevention intervention that would be universally available without creating any new care delivery systems or further burdening the mental health care delivery system.**

**CATCH-IT creates impetus for use of technology-based prevention of mental disorders:** We create a first of its kind method for screening (i.e., adolescents with elevated symptoms of depression), identifying and preventing a major mental disorder in primary care. This approach targets youth at risk for a major mental disorder with what we call an emerging behavioral vaccine. Even partially effective, systematically distributed “behavioral vaccines” could alter illness trajectories and dramatically reduce morbidity and potentially even mortality (suicide). Evolving interventions encompassing true machine learning and integrating biomarker and genotyping data from the primary care electronic medical record with behavioral data, could construct endo-phenotypes and projected trajectories. From these risk prediction and trajectory models, primary care-Internet based interventions could seamlessly deploy Internet/cell phone, peer-to-peer, and professional-to-patient interventions, with the appropriate content, at the appropriate time, in the preferred format, and at the moment most likely to alter trajectories towards resiliency and away from vulnerability.

